#### Ostomy Adjustment Inventory

3.10.3

The scale was developed by Simmons et al. (2009), and the Turkish validity and reliability study was conducted by Karadağ et al. (2011). It is used to understand the adaptation process experienced by individuals with ostomy after a stoma and to determine in which directions this process should be supported. The scale systematically addresses the factors affecting the adaptation of individuals to their new lifestyles. It is a multidimensional scale that evaluates factors related to patients' activities of daily living, emotional adjustment, psychological adjustment, and social isolation. This study evaluated the adaptation of patients with stoma at discharge and 1 month after opening. The scale consists of 23 items and four subscales. The subdimensions are acceptance, anger, anxiety/worry, and social adjustment. The scale items included acceptance (1, 3, 4, 6, 9, 14, 15, 19, 23), anxiety/worry (12, 13, 17, 20, 21), social adjustment (5, 7, 8, 11), and anger (2 and 10). Items 16, 18 and 22 were not included in any subdimension. The 12 items in the scale (2, 5, 7, 8, 10–13, 16–18, 21) are calculated by reversing. The scale items are 5‐point Likert‐type. The response options range from ‘Strongly disagree’ (0) to ‘Strongly agree’ (4). The lowest score is 0, and the highest score is 92. A high score on the scale indicates that individuals have high stoma adaptation. In the validity and reliability study, the Cronbach's alpha (*α*) coefficient value was 0.874 (Karadağ et al. 2011).

### Evaluation of the Data

3.11

The data obtained from the study will be analysed using SPSS 21 (Statistical Package for the Social Sciences) software. First, the demographic and clinical characteristics of the participants will be summarized using descriptive statistics (frequencies, percentages, means and standard deviations). To assess baseline comparability between groups, independent‐samples *t* test will be used for normally distributed continuous variables, Mann–Whitney *U* tests for non‐normally distributed continuous variables, and chi‐square tests for categorical variables.

The primary outcome of the study is state anxiety measured using the State Anxiety Inventory. Changes in state anxiety scores between the intervention and control groups over time will be evaluated using repeated‐measures analysis of variance (ANOVA), including group, time, and group‐time interaction effects. The secondary outcome of the study is postoperative stoma adaptation measured using the Ostomy Adjustment Inventory. Changes in stoma adaptation scores between groups and across follow‐up measurements will also be evaluated using repeated‐measures ANOVA.

Age, gender, diagnosis, stoma type, baseline trait anxiety scores and baseline state anxiety scores will be prespecified as potential covariates. Baseline comparability between groups will be assessed, and adjusted analyses will be performed where clinically relevant imbalances are identified.

All primary analyses will be conducted according to the intention‐to‐treat (ITT) principle. Missing outcome data will be handled using multiple imputation methods. In addition, a per‐protocol analysis including participants who complete all planned assessments will be conducted as a sensitivity analysis. A significance level of *p* < 0.05 will be accepted in all analyses.

Every effort will be made to minimize missing data throughout the study. Reasons for missing data, participant withdrawals, mortality, and stoma closure will be documented and reported in detail. Results will be reported with 95% confidence intervals, effect sizes, and *p* values. The clinical significance of the findings will also be emphasized.

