**Methods:**

A total of 52 patients scheduled for stoma surgery will be randomly allocated to either the intervention group (*n* = 26) or the control group (*n* = 26). The intervention group will receive a structured preoperative stoma simulation in addition to standard care, whereas the control group will receive standard preoperative care alone. The primary outcome is preoperative state anxiety, which will be measured using the Spielberger State Anxiety Inventory 24 h before surgery and on the morning of surgery. The secondary outcome is postoperative stoma adaptation, which will be assessed at discharge and 1 month after surgery using the Ostomy Adjustment Inventory. Data will be collected through face‐to‐face interviews. Outcome assessments will be conducted by a blinded assessor, and statistical analyses will be performed by a blinded statistician.

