### Randomization

3.6

Participants who meet the eligibility criteria and provide written informed consent will be randomly assigned to either the intervention group (*n* = 26) or the control group (*n* = 26) in a 1:1 allocation ratio. A computer‐generated block randomization method with a fixed block size of four will be used to ensure balanced allocation throughout the study.

The randomization sequence will be generated before participant recruitment by an independent researcher who will not be involved in participant recruitment, intervention delivery, outcome assessment, or data analysis.

To ensure allocation concealment, the group assignments will be placed in sequentially numbered, opaque, sealed envelopes prepared by the independent researcher. After participant enrolment and completion of baseline assessments, the intervention researcher will open the next envelope in sequence to determine group allocation. This procedure will be implemented to minimize selection bias and preserve the integrity of the randomization process.

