#### Intervention Group

3.8.2

The stoma care nurse will inform the researcher, who will perform the application of the patients who meet the study criteria. In addition, the stoma care nurse will mark the area where the stoma will be opened with a surgical skin marking pen that is nontoxic, iodine‐free, resistant to rubbing, easy to dry, and suitable for surgical interventions. In addition to routine preoperative care and standard stoma education, patients in the intervention group will receive a stoma simulation intervention. Throughout the study, potential side effects related to the intervention (such as skin irritation, physical discomfort, or psychological distress) will be monitored. If any adverse events occur, the participant will be evaluated by the clinical team, and appropriate support will be provided when necessary. All adverse events will be recorded and reported by the researchers. If serious physical or psychological adverse events related to the intervention are observed, the participant's involvement in the intervention will be discontinued, and the study process will be re‐evaluated by the researchers. For the patients in the intervention group, the researcher will measure their state and trait anxiety levels after informing them about the study and providing written informed consent. A preprepared stoma bag containing wet napkins (information about the contents will be given but not shown to the patients) will be attached to the patient. When the stoma bag is attached to the patient, care will be taken to ensure that it is in the area marked by the stoma nurse. The adapter will be cut into an estimated stoma size, heated by friction of the hands, and adapted to the skin by applying stoma paste. The patient will be asked to put his/her hand on the adapter and apply pressure. Then, the stoma bag is filled with napkins and water, and the adapter will be combined. The patient will be informed that he/she should not hesitate to perform any activity with the stoma bag for 24 h. The patient will be allowed to go to the toilet, eat, sleep, and perform all daily activities with the stoma bag. Brava Adhesive Remover, spray, and Brava Adhesive Remover wipes will be used to clean the adapter adhesives and stoma paste residues on the morning of surgery. The patient's state of anxiety will be measured after the removal of the stoma bag. During the adaptation and removal of the stoma bag to the skin, the steps described in the literature will be followed (American Cancer Society 2019; Kirkland‐Kyhn et al. 2018). It may take time for patients who have had a stoma to adapt. Long‐term follow‐up is necessary for the study results to be more effective. In the literature, evaluating stoma adaptation in patients approximately 1 month after surgery is considered appropriate (Taylan and Aksoy 2021; Zhang et al. 2019; Whiteley et al. 2024). For this reason, stoma adaptations of patients will be evaluated at the time of discharge and 1 month after surgery. If patients have a possible problem with the stoma bag at night before surgery or have questions they want to ask, the information of the 24/7 open phone number where they can contact the researchers will be shared.

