
#### Control Group

3.8.3

As in the intervention group, patients who meet the criteria will be reported to the researchers by the stoma care nurse. The researcher will inform patients, and written informed consent will be obtained. One day before surgery, patients' state and trait anxiety levels will be evaluated. In addition, stoma adaptation of the patients will be evaluated at the time of discharge and 1 month after surgery. Patients in the control group will receive routine preoperative care and standard stoma training provided by a clinical nurse and a stoma care nurse. No additional stoma simulation procedure will be performed in this group.

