### Data Collection

3.9

The data of the study will be collected with the ‘Patient Information Form’, ‘Spielberg State‐Trait Anxiety Scale’ and ‘Adaptation Scale for Individuals with Ostomy’ prepared by the researchers in light of the literature. Before stoma surgery, patients who meet the inclusion criteria will be interviewed and informed about the study. Patients who give verbal and written consent to participate in the study will be included. The ‘Patient Information Form’ and ‘Spielberg State‐Trait Anxiety Scale’ will be applied to the patients 24 h before stoma surgery. The ‘Spielberg State Anxiety Scale’ will be applied on the morning of surgery. The ‘Adaptation Scale for Individuals with Ostomy’ will be applied at discharge and 1 month after surgery (Table 1). The questions in the data collection form will be applied with a face‐to‐face interview technique. Each interview is expected to last approximately 15–20 min. Data will be collected in patient rooms to make patients feel comfortable. During the follow‐up to be performed in the first month after surgery, patients are called to the physician's control in accordance with the hospital protocol. After physician control, the researcher will have a face‐to‐face interview with the patients in the stoma nurse's room and evaluate the stoma adaptation.

**TABLE 1 nop270682-tbl-0001:** Participant timeline: Schedule of enrollment, interventions and assessments.^a^

Timepoint^b^	Trial period					
	Enrollment		Post‐randomization			Close out
	−*t* _ *i* _ to 0	0	*t* _1_ (24 h before surgery)	*t* _2_ (surgery morning)	*t* _3_ (discharge)	*t* _4_ (1 month ±7 days)
Enrollment						
Eligibility screen	X					
Informed consent	X					
[Baseline demographic data]	X					
Randomization		X				
Intervention/comparator						
[Stoma simulation]^c^			X	X (removal)		
[Control]^d^						
Assessments						
[STAI‐trait anxiety]	X			X		
[STAI‐state anxiety]	X			X		
[Ostomy Adjustment Inventory]					X	X

^a^
Recommended content can be displayed using various schematic formats.

^b^
List target timepoints and acceptable time windows in this row (e.g., 30 ± 3 days).

^c^
Arrow indicates continuous delivery of intervention (e.g., drug).

^d^
Example illustrates delivery of comparator at discrete timepoints (e.g., psychotherapy).

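### The primary ANOVA uses the pre-allocation anxiety score as an outcome level and names no deciding effect; ANCOVA of the morning score is sharper and costs nothing

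*Protocol article*

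**What the plan says.** - **Endpoint.** The abstract gives the primary outcome as state anxiety, "measured using the Spielberger State Anxiety Inventory 24 h before surgery and on the morning of surgery".
- **Order of events.** Section 3.6: "After participant enrolment and completion of baseline assessments, the intervention researcher will open the next envelope in sequence". Section 3.8.2 has anxiety measured after consent, then the bag attached and worn, and then: "The patient's state of anxiety will be measured after the removal of the stoma bag".
- **Primary model.** Section 3.11: state anxiety "will be evaluated using repeated‐measures analysis of variance (ANOVA), including group, time, and group‐time interaction effects". The threshold p < 0.05 applies to every analysis. No effect is named as the one that decides.
- **Baseline adjustment.** Section 3.11 also lists baseline state anxiety among the potential covariates. Adjusted analyses follow only where a clinically relevant imbalance is found.
- **Secondary model.** Section 3.11: "Changes in stoma adaptation scores between groups and across" follow-up visits will be evaluated by the same method. The scores are taken at discharge and at 1 month.
- **Sample size.** Section 3.5 uses a two-sided independent-samples t test on one score, with d = 1.29 and power 0.99. This gives 23 per arm, raised to 26 for 10% attrition.
- **Schedule.** The text of section 3.9 places the first state and trait measurement 24 h before surgery; the state scale alone "will be applied on the morning of surgery". Table 1 puts the first STAI in the enrolment column. It shows none at t1, the post-randomisation column labelled 24 h before surgery, and it repeats trait anxiety at t2.

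**The concern.** A score taken before allocation cannot differ between arms except by chance. Making it an outcome level has two consequences.

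First, the three listed effects answer different questions. The time effect says nothing about the intervention. The group effect averages a difference that is zero by design with the real one. The interaction compares mean change between arms. The same data could be positive on one effect and negative on another, and the article does not say which would be reported as the primary result.

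Second, the baseline score has two roles: outcome level in the main model, and covariate in an adjusted model run only on imbalance. Its main use in a randomised trial is to remove variance from the morning score, and that does not depend on whether the arms happen to differ at baseline. The stated plan gives up this precision unless an imbalance appears.

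At stake are the clarity of the primary result and the power to detect an effect smaller than the large one assumed.

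**Working it through.** **Inputs.** Section 3.5 gives means 36.24 (SD 8.15) and 48.16 (SD 10.14), d = 1.29, two-sided alpha 0.05, power 0.99 and 23 per arm after attrition. The correlation rho between the baseline and morning scores is not given, so it is an assumption, varied from 0.2 to 0.8. The SD is taken as equal at both times and in both arms, and the true baseline difference as zero.

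**Step 1: the plan's own figure.** The difference is 48.16 − 36.24 = 11.92. The pooled SD is √((8.15² + 10.14²)/2) = 9.199, so d = 11.92/9.199 = 1.296, in line with the stated 1.29. By the noncentral t distribution, power at 23 per arm is 0.990. Then 46/0.9 = 51.1, which becomes 52 with equal arms. The stated 46 and 52 reproduce.

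**Step 2: what each effect estimates.** Let D be the morning difference, s the SD and d = D/s.

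- Group main effect: compares each patient's mean of the two scores. It estimates (0 + D)/2 with variance s²(1+rho)/2, so the standardised effect is (d/2)/√((1+rho)/2). On the section 3.5 figures it estimates 11.92/2 = 5.96 points.
- Group-time interaction: a t test on change. It estimates D with variance 2s²(1−rho), so the standardised effect is d/√(2(1−rho)).
- ANCOVA of the morning score on baseline: estimates D with residual variance s²(1−rho²), so the standardised effect is d/√(1−rho²).

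**Step 3: power at 23 per arm, d = 1.29.** At rho 0.5 the standardised effects are 0.645/√0.75 = 0.745, 1.29/√1 = 1.29 and 1.29/√0.75 = 1.49.

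| rho | Group effect | Interaction | ANCOVA |
|---|---|---|---|
| 0.2 | 0.79 | 0.92 | 0.99 |
| 0.3 | 0.76 | 0.95 | 0.99 |
| 0.5 | 0.70 | 0.99 | >0.99 |
| 0.8 | 0.62 | >0.99 | >0.99 |

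**Step 4: relative cost of the interaction.** The variance ratio to ANCOVA is 2(1−rho)/(1−rho²) = 2/(1+rho). This is 1.54, 1.33 and 1.18 at rho 0.3, 0.5 and 0.7, and it is the factor by which the interaction needs more patients.

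**Step 5: a smaller true effect.** With d = 0.65, about half the planned value, and rho 0.5, power is 0.58 for the interaction and 0.70 for ANCOVA.

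**Step 6: if either effect could count.** The sum and the difference of two scores with equal variance are uncorrelated. If success could be claimed on the group effect or the interaction, each at 0.05, the type I error would be 1 − 0.95² = 0.0975, about 9.8%. Simulation at 26 per arm gave 0.096 to 0.100.

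**The case against.** The strongest reply is that the plan already implies the right test. Section 3.11 speaks of changes in state anxiety between the groups over time, which in a two-group, two-time ANOVA is the interaction. The list of three effects can be read as a description of the model terms. The interaction is unbiased and undiluted, and at the planned effect with rho of 0.5 or more its power is about 0.99 or higher. An article may also leave the choice of contrast to an analysis plan.

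Most of this stands. A reader might infer that the trial's real power is 0.70, or that its false-positive rate is near 10%. The documents support neither: nothing says that the group effect decides, or that either effect may count. What remains is that the article itself fixes the primary model and the conditional use of baseline, and that this choice is less precise than one available from the same data.

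Three further inferences also fail.

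- **Adaptation.** The article does not make the interaction the test of adaptation. Both scores follow the intervention, so the group effect there is an undiluted test of level.
- **Baseline after allocation.** Section 3.6 and Table 1 both place the baseline STAI before randomisation, and section 3.8.2 does not say that the envelope comes first. The only doubt comes from the label on t1.
- **No morning score for controls.** Section 3.8.3 says that one day before surgery controls' "state and trait anxiety levels will be evaluated" and does not mention the morning. The abstract, section 3.2 and section 3.9 apply the morning assessment to patients generally.

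**Conclusion.** The point holds as an improvement available at no cost, not as an error that invalidates the trial. The stated analysis gives the baseline score the wrong role and leaves the deciding effect implicit. On the reading that the wording favours, the loss is one of precision. It is small at d = 1.29 with rho of 0.5 or more, moderate at lower rho (0.92 at rho 0.2, against a planned 0.99), and larger if the true effect is smaller. The group-effect power and the type I error in steps 3 and 6 apply only if those readings were adopted; they show why the deciding contrast should be named.

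All the power figures for the repeated-measures effects and ANCOVA rest on assumed values of rho, equal SDs and no true baseline difference. The schedule mismatches are minor: the first STAI against the label on t1, and trait anxiety at t2.

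**What to change.** 1. In section 3.11 and the abstract, name the state anxiety score on the morning of surgery as the primary endpoint.
2. Test the arm difference by ANCOVA that always adjusts for the state score taken before the envelope is opened, not only on imbalance. Report the adjusted difference with its 95% CI. This is also closer to the single-score comparison behind the sample size.
3. For adaptation, state that the between-arm difference in level is the test of the hypothesis.
4. Reconcile Table 1 with section 3.9: whether the first STAI belongs to enrolment or to the time labelled 24 h before surgery, and whether trait anxiety is repeated at t2.

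The cost is protocol wording. Both state scores are already planned, and no patients or visits are added. By the date in section 3.1 recruitment has yet to start, so the contrast can be fixed before any data are seen.

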### Sample

3.5

The study will be conducted in an advanced hospital where approximately 9–12 stoma surgeries are performed monthly. The sample size was calculated using G*Power 3.1.9.2. The calculation was based on the primary outcome of the study, state anxiety. The effect size was calculated using the State Anxiety Inventory scores reported by Akbayrak and Uslu (2026), who evaluated the effect of preoperative stoma education including a wearable dummy stoma on postoperative stoma‐related anxiety, adjustment, and self‐efficacy. In that study, the mean State Anxiety Inventory scores were 36.24 ± 8.15 in the experimental group and 48.16 ± 10.14 in the control group. Based on these values, the effect size was calculated as *d* = 1.29. Using a two‐tailed independent‐samples *t* test, *α* = 0.05, power (1 − *β*) = 0.99, effect size = 1.29, and an allocation ratio of 1:1, the minimum required sample size was calculated as 46 participants, with 23 participants in each group. Considering a possible 10% attrition rate during follow‐up, including stoma closure, mortality, or participant withdrawal, the total planned sample size was increased to 52 participants, with 26 participants in each group.

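### Covariate adjustment depends on observed baseline imbalance, with no threshold and no statement of which result decides; fix one ANCOVA in advance instead

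*Protocol article*

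**What the plan says.** All of the relevant text is in section 3.11 (Evaluation of the Data) of the protocol article.

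- **Main model.** State anxiety is analysed by "repeated‐measures analysis of variance (ANOVA), including group, time, and group‐time interaction effects". No covariate is in that model. Stoma adaptation is analysed in the same way.
- **Candidate covariates.** "Age, gender, diagnosis, stoma type, baseline trait anxiety scores and baseline state anxiety scores will be prespecified as potential covariates".
- **Baseline checks.** "To assess baseline comparability between groups, independent‐samples *t* test will be used for normally distributed continuous variables", with Mann–Whitney and chi-square tests for the other variable types.
- **Trigger.** "Baseline comparability between groups will be assessed, and adjusted analyses will be performed where clinically relevant imbalances are identified".
- **Level.** "A significance level of *p* < 0.05 will be accepted in all analyses".

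The article does not define a clinically relevant imbalance. It does not say whether one imbalanced variable brings in only itself or all six. It also does not say whether an adjusted result takes over from the ANOVA or stands beside it.

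**The concern.** The list of candidates is fixed, but the model is not. Which covariates enter, and whether any do, is settled after the baseline data have been seen, against a standard that is not written down.

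Allocation is randomised in blocks of four with no stratification described (section 3.6), so every baseline difference between the arms is chance. A test of that difference asks a question whose answer is already known. What makes a covariate worth including is how well it predicts the outcome, and that does not depend on whether the arms happen to differ on it.

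Two things are at stake. First, two analyses of the primary outcome can exist side by side with no rule on which one decides, which leaves room for selective reporting. Second, a baseline score that is collected anyway is not used in the most efficient way.

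**Working it through.** **The plan's own figure.** The article gives no figure for the adjustment rule. Its sample size provides the planned effect. The SDs combine to √((8.15² + 10.14²)/2) = 9.199, so d = (48.16 − 36.24)/9.199 = 1.296 (stated 1.29). By the normal formula, n per arm = 2 × (1.960 + 2.326)²/1.29² = 22.1, rounded up to 23, or 46 in total. Then 46/0.9 = 51.1, rounded up to 52. The stated 46 and 52 are reproduced.

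**How often the trigger fires under correct randomisation.** With 26 per arm, the standardised difference (SMD) on one covariate has standard error √(2/26) = 0.277. For a threshold s, P(|SMD| ≥ s) = 2 × [1 − Φ(s/0.277)], and for at least one of six it is 1 − (1 − P)⁶. The thresholds are assumptions, since the article gives none.

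| Assumed trigger | One covariate | At least one of six |
|---|---|---|
| p < 0.05 | 0.05 | 1 − 0.95⁶ = 0.26 |
| 0.5 SD | 0.071 | 0.36 |
| 0.25 SD | 0.367 | 0.94 |

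This treats the six as independent and continuous, although gender, diagnosis and stoma type are categorical. With a trait–state correlation of 0.5 the simulated values are 25%, 35% and 92%.

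**What the main model tests.** State anxiety is measured twice before surgery, so the group-by-time term of the ANOVA is the t test on change. Let ρ be the correlation between the baseline and surgery-morning scores. In units of the outcome variance:

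- Change score: 2(1 − ρ) = 1.40, 1.00, 0.60 at ρ = 0.3, 0.5, 0.7.
- ANCOVA: 1 − ρ² = 0.91, 0.75, 0.51.

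ANCOVA has the smaller variance throughout, whether or not the arms are balanced. The article gives no value of ρ, so the range is an assumption.

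**Simulated power at an assumed d = 0.65** (26 per arm; switch from change score to ANCOVA if baseline state anxiety differs by at least 0.25 SD):

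| Analysis | ρ = 0.3 | ρ = 0.5 | ρ = 0.7 |
|---|---|---|---|
| Change score, never adjusted | 0.49 | 0.64 | 0.85 |
| Triggered rule | 0.55 | 0.68 | 0.87 |
| ANCOVA always | 0.66 | 0.75 | 0.89 |

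Repeat runs agree to about 0.01. The triggered rule falls short of ANCOVA by about 0.11, 0.07 and 0.02 to 0.03. The never-adjusted change score falls short by 0.17, 0.11 and 0.04. So the trigger recovers part of a loss that the main model creates. At the planned d = 1.29 every option has power of at least 0.97.

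**Type I error, nominal 0.05.**

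- Fixed ANCOVA: 0.048 to 0.050.
- Trigger followed mechanically: about 0.03 to 0.05, depending on trigger and model, so at or below nominal.
- More favourable of the unadjusted and adjusted results quoted: 0.067 to 0.079.

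**How often the choice matters.** At an assumed d = 0.5, the unadjusted model and a six-covariate model disagree on significance in 23%, 20% and 16% of simulated trials at ρ = 0.3, 0.5 and 0.7.

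**The case against.** The case for leaving the text alone has real substance.

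- **Error rate.** A reader might infer that the rule inflates type I error. It does not if it is applied mechanically. The 0.07 to 0.08 figure requires someone to choose the favourable result, and section 3.11 does not license that. It does not exclude it either, because no mechanical trigger is written down.
- **Power.** A reader might blame the trigger for lost power. Against the ANOVA that the article names, the trigger gains power. The shortfall comes mainly from testing change, and it is negligible at the planned effect.
- **Baseline state anxiety.** A reader might infer that it is ignored unless the arms differ. It is already the first of the two repeated measures, so the interaction uses it, though less efficiently than ANCOVA. For the same reason it cannot sensibly also be a triggered covariate in that model.
- **Trigger almost always available.** This holds at 0.25 SD, which is an assumed threshold. At 0.5 SD or p < 0.05 it does not hold.
- **Supplementary reading.** The ANOVA is tied to the primary outcome and adjusted analyses come in a later paragraph, so they may be meant as secondary. That is a natural reading, but the text does not state it.
- **Blinding.** Section 3.7 has an independent statistician working on Group A and Group B codes. This limits steering towards one arm, but it does not hide which model gives the smaller p value.
- **Detail left to an analysis plan.** A threshold could sit in a document not shown. The dependence on imbalance is itself a stated rule, however, and an analysis plan with one fixed adjusted model would depart from it.

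**Conclusion.** The point holds as a defect in a stated rule. Adjustment depends on chance imbalance, the standard is undefined, and the deciding result is not named. Depending on the threshold assumed, at least one covariate would call for adjustment in about 26% to 94% of correctly randomised trials of this size.

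The harm is mainly room for selective reporting: type I error of about 0.07 to 0.08 if the better of two models may be quoted, against about 0.03 to 0.05 if the rule is followed mechanically. The gain in power from a fixed ANCOVA over the triggered rule is about 0.11, 0.07 and 0.02 to 0.03 at an assumed d = 0.65 and ρ = 0.3, 0.5 and 0.7. That gain would come mainly from replacing the change-score test, and it is negligible at d = 1.29. The documents do not support a claim that the rule as written breaks the error rate or leaves the trial underpowered for its planned effect.

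The change is worth making because it costs almost nothing and recruitment is not planned to start until January 2, 2027 (section 3.1).

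**What to change.** Rewrite the primary-model and covariate sentences of section 3.11 to this effect:

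- The primary analysis is one ANCOVA of surgery-morning state anxiety on group and baseline state anxiety, applied whatever the observed balance. It replaces the two-time repeated-measures ANOVA as the deciding test. Changing only the covariate sentence would leave baseline state anxiety as both a response and a covariate in the same model.
- The stoma adaptation model has no preoperative score to adjust for. It uses a small covariate set named now on prognostic grounds, for example baseline trait anxiety, also applied whatever the balance. The article gives no correlations, so the choice is the investigators' to justify.
- Unadjusted results are labelled supportive.
- Baseline significance tests play no part in deciding adjustment; a descriptive baseline table is enough.

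The cost is the rewording and one or two degrees of freedom. N stays 52 and no new data are needed.
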